### Baseline Data Collection

Baseline questionnaires comprised instruments which have been validated and tested for reliability and were adapted from the 2011 Myanmar Multiple Indicator Cluster Survey [4] 2015, Myanmar census questionnaires [36], the 2011 Demographic and Health Survey, Bangladesh [7], and a 2012 study from Shanghai, China [37]. At baseline, participants were asked to provide information on their socioeconomic status, previous pregnancies and breastfeeding history, knowledge and sources of breastfeeding information, confidence to breastfeed and perceived self-efficacy to breastfeed, intention to breastfeed, and intended breastfeeding patterns.

**Table 1 table1:** Summary of instruments used at various times in the M528 trial.

Instruments	Baseline	Postpartum month					
		1	2	3	4	5	6
Individual socioeconomic factors (participant and husband): age, sex, ethnicity, religion, education, occupation	x						
Household factors: income level, wealth index	x						
Previous pregnancy, childbirth and breastfeeding experience	x						
Breastfeeding knowledge level (high/medium/low)	x						
Intention and confidence to exclusively breastfeed	x						
Breastfeeding self-efficacy scores (high/low)	x	x		x		x	
Postdelivery survey: date of birth; place of birth; type of delivery; and child’s birth, weight, and sex		x					
Child morbidity characteristics: signs and symptoms of fever, cough, respiratory tract infection, diarrhea, dysentery		x		x		x	
Breastfeeding and other feeding follow-up module—24-hour recall and 1-month recall		x	x	x	x	x	x
Social desirability scale (high/medium/low)						x	
Process evaluation on mHealth (intervention group only): frequency of text messages received, user-friendliness of the messages received, perceived relevance of messages, trust in messages, understanding of messages, and new information learned or not							x

We will examine the relationship between breastfeeding duration and self-efficacy using self-report Likert scales (no confidence= 1, somewhat confident= 2, sometimes confident= 3, confident= 4, very confident= 5) [38,39]. With 5 levels of responses to 33 items, total scores range from 33 to 165 and will be categorized as low self-efficacy (1 to 82) and high self-efficacy (83 to 165).

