#### Stage 2: Intervention Service Delivery

The intervention was delivered over 9 months—from recruitment to 6 months postdelivery. Text messages were sent to the intervention group 3 times per week (Tuesday, Thursday, and Saturday) in the evening using CommConnect [35], Telerivet [53], and a local company that has an official contract with mobile operators and experience sending bulk SMS messages. Each text message has approximately 160 characters written in Myanmar fonts (Zawgyi font; Myanmar font systems are not yet standardized but we selected the Zawgyi font because it is the most commonly used font in Myanmar). If a participant withdrew or experienced the death of their child, we stopped messaging. The numbers of messages received were the total number of weeks in the study × the number of messages sent per week. The total number of weeks was 38, assuming that the participant was recruited at 28 weeks’ gestation, delivered at 40 weeks (term pregnancy), and remained in the study until the child reached 6 months. Therefore, the intervention group received up to 114 text messages. All participants received the usual hospital antenatal, intra- and postpartum care, and infant feeding support regardless of their assigned group. See Figure 3 for example text message.

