### Process Evaluation

An evaluation of the use of mobile phones to promote breastfeeding practices was conducted with participants from the intervention group. Information on text delivery success, user experiences (user-friendliness), acceptability (trust), comprehension, new information learned, and feedback from received messages was assessed by trained callers during phone calls at 5 to 6 months after delivery. We measured acceptability (proportion of participants who trust the messages), comprehension (proportion of participants who can describe the last message received), and new information learned (proportion of participants who indicate they learned new information about breastfeeding). These instruments have been widely used in mHealth evaluations in other countries [20,57-60] and took about 10 minutes to administer.

At completion, a qualitative study was conducted with intervention group participants. Based on information from follow-up calls, participants were split into 3 subgroups: EBF for 6 months, predominant and other types of breastfeeding (excluding EBF), and breastfed for less than 1 month only. In-depth interviews were held with approximately 25 women (7 to 9 women from each group) using semistructured guidelines. We explored user experiences in receiving SMS text messages, perceptions about the number of messages received, message delivery success, acceptance of the service delivery model, and effect of messages on breastfeeding practices. We expected that this number of participants would allow us to reach saturation point [60]. There were variations in the numbers of participants we could interview based on breastfeeding outcome, participant’s availability, logistic reasons, and feasibility of the study.

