### Data Analysis

Quantitative data were collected via tablets and automatically submitted to the Dimagi server from which we could monitor data and generate reports. Stata software version 13 (StataCorp LLC) was used for data analyses. The intervention and control group outcomes will be compared using intention-to-treat principles [61]. Descriptive analyses were used to summarize participant baseline characteristics and breastfeeding practices. Likert scales were analyzed using Mann-Whitney U tests or cumulative odds ratios and proportions between groups using chi-square tests. Duration of EBF was compared by survival analyses with log-rank tests for between-group comparisons. If differences in baseline characteristics of the groups are identified, multivariable analyses will be undertaken. We report results using the CONSORT guidelines for reporting of randomized trials [62]. As follow-up data collection had to rely on the mothers’ self-reporting alone, we adjusted the potential social desirability bias [43] in our analyses to confirm the accuracy of self-reported outcome measures.

For process evaluation, we used Stata software for survey data analysis. We conducted descriptive analyses to summarize participant baseline characteristics and their experiences and feedback about receiving text messages. Text message delivery success was measured by the frequencies of messages received, and proportions were compared with chi-square tests. For the qualitative study, we used thematic analysis. All digitally recorded interviews were transcribed verbatim in Burmese in Microsoft Word and were reviewed to check for accuracy and translated to English. A list of thematic codes was developed by MPH, which was independently reviewed and verified by AA. The data were then be manually coded by MPH for emerging themes, which were again verified by other investigators and the most relevant themes are summarized in a document.

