## Discussion

### Implications of the Research

We hope to achieve our outcomes as SMS text messaging is increasingly being applied to improve reproductive, maternal, neonatal, and child health with growing evidence of its effectiveness [20-28,31,32,59,60]. This study is important as our intervention will leverage the power of mobile phone technology at an appropriate time following the opening up of the telecommunications market in Myanmar. Incorporating feedback from the community and mobile service providers prior to the study was a key element in the study design. We could envisage similar larger scale interventions implemented within the health system with women recruited from other public and private hospitals or community settings in the future. We also acknowledge that a number of factors may interfere with the success of the intervention. We anticipate the possibility of mobile coverage variation across geographic areas as the launch of mobile operators only started in 2014. Another barrier is that people often change phone numbers in order to receive better network and promotional prices leading to difficulties in sending text messages and making follow-up phone calls. Successfully upscaling the intervention would have the potential to improve child nutrition and consequently to reduce neonatal and infant morbidity and mortality where causes are associated with suboptimal breastfeeding practices. With the endorsement of Sustainable Development Goals, nutrition is central to 12 of the 17 development goals [63] and the role of breastfeeding is essential in achieving these goals. We also anticipate that continued growth in the coverage of the mobile network could attract the Ministry of Health and Sports and policy makers to implement mHealth-based behavior change interventions in national programs.

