Another limitation is that there may be technological challenges when participants are not familiar with the use of mobile phones. However, we have compensated for this by providing training. As with other mobile phone programs, we anticipate a possible low response rate because participants may not answer calls, may switch off their phone, or may change their phone number. Solutions to these problems include recording alternate contact numbers during recruitment, calling repeatedly if the phone is powered off, or trying to reach the participant based on the suggested time to call.

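### Text delivery success rests on late phone self-report from intervention women who could be reached, so it is probably overstated, and the planned message contrast between arms goes unchecked

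*Protocol article*

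**What the plan says.** **Measure.** Data Analysis defines the quantity and its analysis: "Text message delivery success was measured by the frequencies of messages received, and proportions were compared with chi-square tests".

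**Source and timing.** Process Evaluation lists text delivery success among the items for which information "was assessed by trained callers during phone calls at 5 to 6 months after delivery".

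**Population.** The same section says: "An evaluation of the use of mobile phones to promote breastfeeding practices was conducted with participants from the intervention group". Table 1 agrees and lists the item as "Process evaluation on mHealth (intervention group only): frequency of text messages received". In-depth interviews with about 25 intervention women also touch on delivery, but they are qualitative, and the women were grouped using information from follow-up calls.

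**Threats the article names.** Under Implications of the Research, frequent changes of phone number are described as "leading to difficulties in sending text messages and making follow-up phone calls". Under Strengths and Limitations: "we anticipate a possible low response rate because participants may not answer calls, may switch off their phone, or may change their phone number". The remedies offered there include alternate contact numbers and repeat calling.

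**Stopping rule and planned counts.** Stage 2: Intervention Service Delivery says: "If a participant withdrew or experienced the death of their child, we stopped messaging". It gives up to 114 messages for the intervention group, sent through CommConnect, Telerivet and a local bulk-SMS company. Control Group gives an estimated 38 messages per control participant.

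**The concern.** A delivery measure should cover the women to whom messages were addressed. This one covers those who answered a call many months later. By the article's own account, a changed number interferes with the text and with the call alike, so being available for the survey is linked to the quantity the survey measures.

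Two things are at stake. First, the Conclusions promise evidence on whether text messaging is effective and feasible, and the Discussion looks ahead to larger programmes; how many messages arrived is part of feasibility. Second, if the feeding result is null, a sound delivery figure is needed to tell an ineffective intervention from one that was not delivered.

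In addition, because only one arm is asked about receipt, no data described in the article confirm the difference in message exposure between arms.

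**Working it through.** **1. Is there a figure to reproduce?** The article states no delivery rate and no survey response rate. The only figures on exposure are planned counts. They reproduce, but as schedules: 38 weeks × 3 per week = 114 (intervention) and 38 weeks × 1 per week = 38 (control). Stage 2 describes the number received as weeks in the study multiplied by messages sent per week. That is a count of messages scheduled, and it equals receipt only if every message arrives.

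**2. Form of the bias.** Let L be the share of intervention women not surveyed, S the proportion of messages delivered among those surveyed, and M the proportion among those not surveyed.

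- Delivery over all intervention women = (1 − L) × S + L × M
- Overstatement by the survey = S − [(1 − L) × S + L × M] = L × (S − M)

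This is positive when M < S, zero when M = S, and negative when M > S. The stated effect of number changes on both texts and calls makes M < S the likely case.

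**3. Inputs.** L = 13% is borrowed from Sample Size Determination, where it is the allowance for loss over the whole trial and not a survey non-response rate. With 353/2 ≈ 176 women per arm it corresponds to about 23 women. S and M are assumptions, as are the other values of L.

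**4. Results.** Example: S = 90%, M = 25%, L = 13% gives 0.87 × 90% + 0.13 × 25% = 81.6%, so the survey figure is 8.5 points too high (0.13 × 65 = 8.45).

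Overstatement in percentage points:

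| L | S 80%, M 50% | S 80%, M 25% | S 80%, M 0% | S 90%, M 50% | S 90%, M 25% | S 90%, M 0% |
|---|---|---|---|---|---|---|
| 5% | 1.5 | 2.8 | 4.0 | 2.0 | 3.3 | 4.5 |
| 13% | 3.9 | 7.2 | 10.4 | 5.2 | 8.5 | 11.7 |
| 20% | 6.0 | 11.0 | 16.0 | 8.0 | 13.0 | 18.0 |
| 30% | 9.0 | 16.5 | 24.0 | 12.0 | 19.5 | 27.0 |

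At L = 13% the range is about 4 to 12 points. In every row it falls to 0 if M = S.

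**5. The chi-square comparison.** Data Analysis attaches chi-square tests of proportions to the delivery measure. Table 1 restricts the receipt item to the intervention group. A test of receipt therefore cannot be between arms, and the article names no other grouping.

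**The case against.** The strongest objections are these.

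- **The size is assumed.** This stands. No delivery or response rate is given, and recall error could move the figure in either direction. A reader might infer that overstatement is established; the article supports only that it is likely.
- **Many women who changed number were probably still reached.** Feeding calls were monthly, and alternate numbers and repeat calls were used. This stands in part: it lowers L and brings some low-receipt women into the survey. One might reply that alternate numbers rescued the calls but left the messages going to a dead number, but the article does not say whether messages were redirected.
- **Withdrawal and child death are not delivery failures.** This stands. Messaging then stopped by rule, so these women are not evidence of overstated delivery unless the denominator is defined to include them.
- **Causes are not ranked.** This stands. A reader might take number changes and poor coverage together as the main cause of failure. The article calls number change another barrier and links failed calls to that alone, and eligibility required residence in a covered area.
- **A journal article condenses, and sending logs may also have been used.** This does not remove the point. The article does not leave the measure open: it fixes the item, source, timing and arm.
- **The consequence is small.** Delivery is neither a primary nor a secondary outcome, and the article discloses the contact problems. This limits the weight of the point, but the disclosure does not correct the measure. The article also promises no comparison of receipt between arms; the point is that exposure in the control arm goes unchecked.

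**Conclusion.** The point holds as a limited one. Delivery success, as the article fixes it, is measured in a sample whose membership depends partly on the same problem that stops messages arriving, so a likely upward bias should be expected. Its size cannot be derived from the article. At 13% not surveyed it is about 4 to 12 percentage points for assumed delivery of 80–90% among surveyed women and 0–50% among the rest, and it disappears if the two groups received messages equally. Receipt in the control arm is not measured, so the planned contrast of up to 114 versus about 38 messages rests on the schedule alone.

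A reader might go further and infer that the trial's main result is compromised. It is not: the effect is confined to the process and feasibility conclusions, and the intention-to-treat comparison of exclusive breastfeeding does not use this measure.

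**What to change.** Take delivery success from the sending records of CommConnect, Telerivet and the bulk-SMS company, where these were retained.

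- For every randomized woman in both arms, count messages scheduled, sent, delivered and failed up to the date messaging stopped, and report delivered over scheduled by arm.
- Tabulate stops for withdrawal or child death separately, and do not count them as delivery failures.
- Report the survey figure beside this, with its denominator and response rate, and keep the survey for trust, comprehension and new learning.
- State which groups the chi-square test of receipt compares.

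The cost is a data export and a short tabulation, with no new contact with participants; the article says analysis is still under way. The drawback is that operator receipts may be incomplete, and they do not show that a message was read. If no records survive, report the survey result as receipt among women reached, with the range above as a sensitivity statement.

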## Results

The targeted 353 pregnant women were recruited between January and March 2015. Baseline data have been collected. SMS messages have been developed, pretested, and sent to the women from both groups. Follow-up data collection via phone calls is now complete. Data analysis is still ongoing and results are to be expected soon. This is the first RCT study examining the effects of mobile text messages in promoting EBF.

## Discussion

### Implications of the Research

We hope to achieve our outcomes as SMS text messaging is increasingly being applied to improve reproductive, maternal, neonatal, and child health with growing evidence of its effectiveness [20-28,31,32,59,60]. This study is important as our intervention will leverage the power of mobile phone technology at an appropriate time following the opening up of the telecommunications market in Myanmar. Incorporating feedback from the community and mobile service providers prior to the study was a key element in the study design. We could envisage similar larger scale interventions implemented within the health system with women recruited from other public and private hospitals or community settings in the future. We also acknowledge that a number of factors may interfere with the success of the intervention. We anticipate the possibility of mobile coverage variation across geographic areas as the launch of mobile operators only started in 2014. Another barrier is that people often change phone numbers in order to receive better network and promotional prices leading to difficulties in sending text messages and making follow-up phone calls. Successfully upscaling the intervention would have the potential to improve child nutrition and consequently to reduce neonatal and infant morbidity and mortality where causes are associated with suboptimal breastfeeding practices. With the endorsement of Sustainable Development Goals, nutrition is central to 12 of the 17 development goals [63] and the role of breastfeeding is essential in achieving these goals. We also anticipate that continued growth in the coverage of the mobile network could attract the Ministry of Health and Sports and policy makers to implement mHealth-based behavior change interventions in national programs.

### Strengths and Limitations

A key strength of our study is the use of an RCT design to assess the impact of text messages on improving breastfeeding practices. Although the trial cannot be fully blinded, research team members who recruit participants and conduct follow-up phone calls are blinded to group allocation. By sending messages with different content to both control and intervention groups, we reduce the possibility of indirect effects of participants receiving health messages on the targeted behaviors. Both groups receive pregnancy and child healthcare-related text messages, but only the intervention group receives messages about breastfeeding. The intervention is feasible to implement because of the significantly reduced prices of subscriber identity module (SIM) cards, increased availability of cheap smart phones, and improved coverage of a 3G network. In addition, female literacy is high with 94% of urban women and 84% of rural women able to read text messages [36]. The timing of the study may allow new investments for mHealth-based EBF promotion interventions.

Limitations include recruitment from only 1 hospital, which will reduce the generalizability of results. To date, only major cities in Myanmar have reliable access to the mobile network but this is changing rapidly as the network is expanded, offering opportunities to adapt the intervention for rural populations. The hospital selected for recruitment, which has a patient population of women from diverse ethnic and socioeconomic backgrounds, is the largest public hospital providing free quality delivery care service. Women come from all over the country, including from rural and urban slum areas. It is likely that the participants have similar feeding practices to women from other areas as feeding practices only differ slightly between states and regions [4]. We acknowledge that the intervention group has more frequent SMS text messages than the control group and it could be a limitation of the study. However, we assume that the difference in SMS text message frequency might not constitute an intervention. Several studies including studies conducted in Australia [22], Iran [64], and Korea [65] delivered text messaging service once a week to the intervention groups and findings reported that these interventions were effective.

Another limitation is that there may be technological challenges when participants are not familiar with the use of mobile phones. However, we have compensated for this by providing training. As with other mobile phone programs, we anticipate a possible low response rate because participants may not answer calls, may switch off their phone, or may change their phone number. Solutions to these problems include recording alternate contact numbers during recruitment, calling repeatedly if the phone is powered off, or trying to reach the participant based on the suggested time to call.

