### Recruitment, Assignment, and Allocation

Participant eligibility was assessed via a hospital attendance registry (used by hospital staff) and antenatal care records (kept by the participant) in which information such as age, weeks of gestation, address, and phone numbers were recorded. At recruitment, researchers identified potential participants with the help of hospital nurses, explained the study, provided an information statement and consent form written in Burmese, and confirmed eligibility. If a woman agreed to participate, informed consent was obtained, and she was requested to complete the baseline survey questions. The participant’s mobile phone was checked for compatibility with text messages and, if needed, brief training on how to read and send text messages was provided. The recruitment process took 6 weeks (January to February 2015). Out of a total of 450 potentially eligible pregnant women, 353 were confirmed to be eligible and consented to participate in the trial. Each woman received 500 Myanmar kyats (US $0.50) to compensate for sending a text message to inform the research team of her delivery date.

Eligible women were randomized to the intervention or control group according to an allocation sequence generated by a computer program [34] with a block size of 16 to ensure a balanced group size. Each study and group number was kept in an opaque envelope to conceal the allocation sequence and securely stored. At recruitment, research team members sequentially took an envelope for each consenting participant and conducted the baseline interview. After the participant’s information was recorded, the envelope was opened and the group allocation was recorded.

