### Blinding

Because the intervention could not be blinded, we minimized bias by ensuring both groups received messages and by not explaining in the consent and information sheets how the text messages differed between groups. The information statement provided only general information that each participant could be allocated randomly into a group; would receive messages containing information on pregnancy, childcare, and breastfeeding practices; and that the frequency of messages could vary from 1 to 3 times per week. Research staff and interviewers (via telephone) were blinded to each participant’s group status although they might guess the group based on participants’ responses. To minimize bias, we also blinded research staff to the trial aims and hypotheses.

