### Intervention Procedures

Before the start of the trial, research team members received training by the principal investigator on how to collect data by tablet, conduct recruitment, implement group allocation, conduct follow-up phone calls, and monitor times to call participants. The schedule of enrollment, interventions, and assessments is shown in Table 2.

**Table 2 table2:** Protocol schedule of enrollment, intervention, and assessments for M528 (average length of study duration is 36-38 weeks).

		Women at 28-34 weeks gestation	1 day after enrollment	At 36 weeks	Delivery	Age of child in months					
**Enrollment**						1	2	3	4	5	6
	Eligibility assessment, consent, assignment, and allocation	x									

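### Recruiters and phone interviewers are said to be blinded to allocation, but the envelope procedure and a caller-run survey given only to the intervention group contradict this

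*Protocol article*

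**What the plan says.** Two places in the protocol article claim staff blinding.

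- Strengths and Limitations first accepts that the trial cannot be fully blinded, then says that "research team members who recruit participants and conduct follow-up phone calls are blinded to group allocation".
- Blinding says that research staff and telephone interviewers "were blinded to each participant’s group status although they might guess the group based on participants’ responses". It adds that staff were not told the trial's aims or hypotheses.

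Four places describe procedures that bear on the claim.

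- Recruitment, Assignment, and Allocation: "At recruitment, research team members sequentially took an envelope for each consenting participant and conducted the baseline interview". Once her information was recorded, "the envelope was opened and the group allocation was recorded".
- Intervention Procedures: research team members were trained to "conduct recruitment, implement group allocation, conduct follow-up phone calls", among other tasks.
- Process Evaluation: information on message delivery, trust, comprehension and new learning "was assessed by trained callers during phone calls at 5 to 6 months after delivery". Only intervention participants took part.
- Table 1 labels the row "Process evaluation on mHealth (intervention group only" and marks it under month 6. Table 2 also puts the survey at month 6, beneath the follow-up phone calls.

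**The concern.** Opaque envelopes opened after the baseline interview conceal allocation up to enrolment. They do not blind anyone present when the envelope is opened. Likewise, a caller cannot give a survey reserved for one arm without knowing which arm the woman is in. The article concedes that staff may guess from what women say, but here knowledge of the arm comes from the trial's own procedures.

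This matters because, according to Data Analysis, feeding is known only from what the mother reports. The women cannot be blinded, so interviewer blinding is one of the main protections the design can offer. The planned social desirability adjustment deals with the respondent's tendency to please. It does not deal with what the caller knows, or with questions put to one arm only. A reader who takes the strengths paragraph at face value would credit a protection that the described design lacks.

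**Working it through.** The article gives no figure on this point, so the check is a comparison of its statements, followed by an illustration of scale.

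**1. Recruiters.** Recruiting staff take the envelope and conduct the interview; the envelope is then opened and the group written down. Training for the research team includes implementing allocation. No separate envelope opener is described. On the plain reading, staff involved in recruitment learn the allocation, yet Strengths and Limitations says that those who recruit are blinded to it.

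**2. Callers.** The process survey is for the intervention group only and is given by trained callers by telephone. It asks women to describe the last message received and whether they learned anything new about breastfeeding. Only the intervention group receives breastfeeding messages. Anyone giving the survey therefore knows the arm, and its content also sits badly with keeping staff unaware of the aims. At 1:1 allocation this concerns up to 353/2, or about 176, women.

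**3. Timing.** Feeding is recorded monthly at 1 to 6 months.

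| Source | When the process survey is placed |
|---|---|
| Process Evaluation | 5 to 6 months after delivery |
| Tables 1 and 2 | Month 6 |
| Abstract, Introduction, Data Collection | End or completion of the study |

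On any of these, the survey comes after the month 4 call, so months 1 to 4 are free of it. At months 5 and 6 the order of the feeding module and the survey is not stated. The envelope route differs: it could touch any month, but only where someone who saw a woman's allocation later took her feeding reports.

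**4. Scale, under an assumption not in the documents.** Let a fraction f of intervention women who are not exclusively breastfeeding be recorded as doing so at month 6, with no such error in controls. The added difference is f × (1 − p), where p is the true intervention rate. With f = 5%:

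- p = 15% (no true effect): 0.05 × 0.85 = 0.0425, or 4.3 points
- p = 30% (the hypothesised rate): 0.05 × 0.70 = 0.035, or 3.5 points

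The target difference is 30% − 15% = 15 points.

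With no true effect, 15% in both arms and 156 per group (the evaluable number in Sample Size Determination), the chance of a significant result favouring the intervention is Φ((d − 1.96·s0)/s1). Here d = 0.85f, and s0 and s1 are the pooled and unpooled standard errors of the difference.

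| f | Recorded intervention rate | Chance of a significant result |
|---|---|---|
| 0 | 15.0% | 2.5% (nominal) |
| 2% | 16.7% | 6% |
| 5% | 19.25% | 17% |
| 10% | 23.5% | 48% |

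For f = 5%: s0 = √(2 × 0.17125 × 0.82875/156) = 0.0427; s1 = √((0.15 × 0.85 + 0.1925 × 0.8075)/156) = 0.0426; (0.0425 − 1.96 × 0.0427)/0.0426 ≈ −0.97, giving 17%.

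These figures fit a month 6 prevalence, for which every woman not exclusively breastfeeding could be misrecorded. For the Abstract's outcome, exclusive breastfeeding from birth to 6 months, a woman already recorded as non-exclusive cannot be converted by a late report, so the shift would be smaller.

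**The case against.** The strongest reply is that the text leaves room for more blinding than it spells out. Several parts of it stand.

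- The sentence on opening the envelope is passive and names no opener. The envelope held a study and group number, and a number need not have told staff which arm was which.
- The training sentence lists tasks for the team as a whole. A reader might infer that the person who opened a woman's envelope later took her feeding reports; the article does not say so. Nor does it say outright that the survey callers were the outcome callers. A condensed article may leave staffing details to the full protocol.
- A reader might also infer that intervention women were prompted about breastfeeding messages at month 5, before reporting at month 6. Only Process Evaluation mentions month 5. If the survey followed the feeding module in the month 6 call, that woman's outcome was already recorded and priming was impossible.
- The article concedes guessing and incomplete blinding, withholds the hypotheses from staff, and adjusts for social desirability.

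These points limit what can be said about bias. They do not rescue the claim. The finding is not that staffing details are absent, but that blinding is asserted without exception beside procedures that disclose the arm. An intervention-only survey does so whoever opened the envelopes.

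**Conclusion.** The claim of recruiter and caller blinding does not hold as worded. For callers who gave the process survey, the contradiction follows directly from the schedule. For recruiters, it rests on the plain reading that those who held the envelope and ran the interview learned the group when it was opened.

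The documents do not support the stronger conclusion that the result is biased towards the intervention. Bias at months 5 and 6 is possible, and depends on who made the calls and in what order the modules were completed. The survey cannot have affected months 1 to 4. The 3.5 to 4.3 points and the 6%, 17% and 48% illustrate assumed misreporting rates; they are not estimates for this trial.

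**What to change.** - Correct Blinding and Strengths and Limitations to say that staff who opened envelopes or gave the process survey were not blinded to those women's allocation. Stop listing full recruiter and caller blinding as a strength.
- Report from the tablet records, if retained, who made the calls and whether the month 5 and month 6 feeding modules were completed before the survey.
- As a sensitivity analysis on existing data, show the between-group comparison of exclusive breastfeeding at month 4, before any process survey, beside month 6. Use all randomised women in both arms. Do not drop reports taken after the survey: only the intervention arm was surveyed, so this would remove outcomes from one arm on a post-randomisation event.

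The month 4 comparison addresses the survey route only. A change between months 4 and 6 could also be a real change in feeding, so it should be read as context and not as a test for bias. Follow-up calls are complete, so a rule on the order of modules can no longer help this trial.

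The cost is a less favourable blinding statement and a little extra analysis, with no new data collection.
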